**Methods:**

This is an interventional study in which the effects of vitamin D supplementation on plasma vitamin D levels, inflammatory and antioxidant biomarkers and factors associated with cell proliferation, differentiation, damage, and apoptosis will be investigated stratified by variations in *VDR* genotype. The present study will be conducted on breast cancer survivors referred to the Shohadaye Tajrish hospital and its associated clinics. One hundred ninety-eight breast cancer survivors will receive 4000 IU of vitamin D3 daily for 12 weeks. *VDR* Fok1, ApaI, TaqI, BsmI, and Cdx-2 genotype will be determined at the end of the study and responses to vitamin D supplements (inflammatory, antioxidant, cell proliferation, differentiation, damage, and apoptosis biomarkers) will be compared between the three subgroups of each *VDR* polymorphism as well as different *VDR* haplotype categories.

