## Objectives

### Primary objectives

To compare plasma 25-hydroxy vitamin D_3_(25(OH) D_3_) within and between polymorphic groups (Fok1, Bsm1, Taq1, Apa1, and Cdx2) in breast cancer survivors, adjusted for potential confounders.To compare plasma 25-hydroxy vitamin 25(OH) D_3_within and between haplotype groups in breast cancer survivors, adjusted for potential confounders.

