### Statistical analyses

We will check the distribution of variables using the Shapiro–Wilk test. The genetic factors, Apa-I, Fok1, Taq-I, Bsm1, and Cdx2, will be considered as the main exposures. To check the within-factor differences in case of normality, we will use one-way ANOVA, and for skewed (non-normal) variables, we will use the Kruskal–Wallis *H* test.

To assess the effect of each category of exposures on outcomes of interest, we will use multiple linear regression. We will log-transform all of the non-normal variables and compute the differences for all response variables (25(OH)D3, BMI, WC, HC, fat mass, TNFα, IL6, hs-CRP, PAI-1, Bcl2, SOD, TAC, MDA, 8-OHdG, MMP9, IFNβ, E-cadherin, sICAM, and sVCAM,) from second and baseline follow-up. All analyses will be adjusted for potential confounders, including energy, fat, carbohydrate and protein intakes, physical activity, sun exposure, and 25(OH)D3 at baseline. The significant effect of the coefficients of different categories of genetic factors will be checked; we will use cluster robust standard errors because of repeated measurements on each subject.

Deviation from Hardy–Weinberg equilibrium for each SNP will be determined using Fisher’s exact test, performing by the HWE exact function in the R package “genetics.” Deviation from Hardy–Weinberg equilibrium for each SNP will be determined using “genhwi” command in Stata. Haplotypes frequencies and distributions will be estimated using the Haplo.em, the haplo.stats software package in the R [30]. The association of haplotypes with outcomes of interest will be tested using the means of the haplo.glm function of the R package “haplo.stats.”

We will use Stata 14.0 (StataCorp. 2015. Stata Statistical Software: Release 14. College Station, TX: StataCorp LP.), and R Statistical software (R Core Team (2017). R: A language and environment for statistical computing. R Foundation for Statistical Computing, Vienna, Austria. URL https://www.R-project.org/.).

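### The primary 25(OH)D3 question is judged coefficient by coefficient over five co-equal SNPs, plus haplotypes; if each test is at 5%, the chance of a false genotype claim is roughly one in three (about 25–50%)

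*Protocol article*

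**What the plan says.** The protocol article has two primary objectives, both on plasma 25(OH)D3. The first compares it "within and between polymorphic groups (Fok1, Bsm1, Taq1, Apa1, and Cdx2) in breast cancer survivors, adjusted for potential confounders". The second compares it "within and between haplotype groups in breast cancer survivors, adjusted for potential confounders".

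Under Statistical analyses, the genetic factors "Apa-I, Fok1, Taq-I, Bsm1, and Cdx2, will be considered as the main exposures". Three elements of that section bear on inference:

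- An unadjusted test for each factor: "To check the within-factor differences in case of normality, we will use one-way ANOVA", with Kruskal–Wallis for skewed variables.
- A multiple linear regression of the change in each response, adjusted for diet, physical activity, sun exposure and baseline 25(OH)D3, with cluster-robust standard errors. Its decision step is: "The significant effect of the coefficients of different categories of genetic factors will be checked".
- For haplotypes: "The association of haplotypes with outcomes of interest will be tested using the means of the haplo.glm function".

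The abstract gives the number of categories. Responses "will be compared between the three subgroups of each *VDR* polymorphism as well as different *VDR* haplotype categories".

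The text available names no lead SNP, no ranking of the two primary objectives, no significance level and no rule for combining the tests. Fok1 is singled out only in the sample-size note, where its allele frequency is given.

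**The concern.** The regression step fixes how a genotype effect is to be recognised: by the significance of individual category coefficients. With five SNPs on an equal footing, one outcome has ten chances to produce a positive result, and the haplotype objective adds more. The Hypothesis section says that response will vary between polymorphic groups, but not which or how many coefficients must show it. A single small p-value among many could therefore be reported as confirmation.

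This matters more here than in a two-arm trial. The Discussion acknowledges that there is no control group, so the comparison between genotypes carries most of the inferential weight. The Discussion also says that, if VDR SNPs modify the response, the results will inform genotype-based vitamin D requirements. A chance finding on one SNP would feed directly into that use.

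**Working it through.** **Inputs from the protocol article.** Five SNPs; three genotypes each; two primary objectives on 25(OH)D3; 55 per group; three groups; 20% dropout; 198 recruited; Fok1 minor allele frequency 0.3285.

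**The plan's own figure.** It states no error rate. Its sample size reproduces: 55 × 3 = 165, and 165 × 1.20 = 198. A 20% loss from 198 leaves 198 × 0.8 = 158.4.

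**Assumptions.** 5% two-sided per test, since no alpha is visible and the sample-size assumptions sit in Fig. 1, which was not available. Allele frequencies for the other four SNPs, and all linkage between SNPs, are also assumed.

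**Step 1: number of coefficients.** Three genotypes give two non-reference coefficients, so 5 × 2 = 10.

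**Step 2: benchmarks under independence.**

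- Two tests (one SNP): 1 − 0.95² = 9.8%
- Five tests: 1 − 0.95⁵ = 22.6%
- Six tests: 1 − 0.95⁶ = 26.5%
- Ten tests: 1 − 0.95¹⁰ = 40.1%

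**Step 3: simulation with no genotype effect.** The coefficients are correlated, because the two within a SNP share a reference group and SNPs may be linked. Data were therefore simulated under the null (6,000 runs, Monte Carlo error about 0.6 points, ordinary standard errors, no covariates, haplotype phase known for Bsm1–Apa1–Taq1). Linkage within those three SNPs was varied from none to complete. Entries are the chance of at least one false positive on 25(OH)D3 for N = 198 / N = 165.

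| Tests counted | No linkage | Intermediate | Three SNPs fully redundant |
|---|---|---|---|
| Any of 10 coefficients at 5% | 38.2% / 37.9% | 33.6% / 33.4% | 24.4% / 25.8% |
| The 10, or any haplotype coefficient, at 5% | 49.8% / 49.7% | 38.5% / 38.6% | 24.7% / 26.1% |
| Five joint 2-df tests at 5% | 22.6% / 21.8% | 20.6% / 19.0% | 13.8% / 14.0% |
| Five joint tests and one global haplotype test at 5% | 25.1% / 24.0% | 22.7% / 21.3% | 15.9% / 16.2% |
| Five joint tests at 1% | 5.0% / 5.0% | 4.6% / 4.4% | 3.0% / 2.7% |

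**Step 4: sensitivity at n = 158** (3,000 runs, other assumed allele frequencies). Any of ten coefficients gave 39% with independent SNPs, falling to 30% when three SNPs were nearly identical. With robust standard errors, which the plan specifies, the figures were 41% and 33%. Five joint tests gave 16–23% with ordinary and 20–26% with robust standard errors. For one SNP alone, the chance that either coefficient is significant was about 9–10%.

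The separate ANOVA or Kruskal–Wallis tests are not counted in any of these figures. Counting them could only raise the rates.

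**The case against.** The strongest reply is that a multiplicity rule is commonly left to the full protocol or the analysis plan, and neither is shown. That stands: the absence of an adjustment is not by itself an error, and no sentence in the article says that tests will be unadjusted or made at 5%. What remains is a rule that the article does state. Checking category coefficients inflates error even within one SNP (about 9–10% instead of 5%), and a later correction across SNPs would not by itself repair that.

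Second, the article does name one overall test per factor, the ANOVA or Kruskal–Wallis. A reader might infer that no single test per SNP exists, and that would be wrong. But this test does not carry the confounder adjustment that the primary objectives ask for, and nothing makes the coefficients conditional on it. If an overall test did govern, the rate would be about 14–26%, not one in three.

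Third, a reader might infer that the plan declares success on any significant coefficient, or that one in three is a minimum. The article says neither. The any-of-ten reading is an inference from a loosely worded hypothesis, and strong linkage brings the rate down to about one in four.

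Fourth, one could multiply the 19 listed responses by 10 coefficients and quote 190 × 0.05 = 9.5 expected false positives. The arithmetic is right, but 18 of those responses are not the primary outcome, and the Secondary objective section already calls the mean-change analyses investigational.

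**Conclusion.** The point holds in limited form. The article's analysis section judges the primary response by individual genotype coefficients over five co-equal SNPs, and a second primary objective covers haplotypes. Nothing in the text ranks or combines these tests.

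If each test is made at 5% and any significant coefficient is read as a genotype effect, the chance of at least one false claim on 25(OH)D3 is roughly one in three, with a range of about 25–50%. The low end needs three fully redundant SNPs; the high end needs no linkage and counts haplotype coefficients. One joint test per SNP at 5% narrows this to about 14–26%, still well above 5%.

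The figures rest on the assumed 5% level, the any-coefficient reading, and assumed linkage and allele frequencies (only that of Fok1 is given). Even the lowest figure for the coefficient rule is about five times 5%, so the conclusion does not depend on the exact value.

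**What to change.** For 25(OH)D3:

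1. Use one covariate-adjusted test per SNP: either the joint 2-df test of both genotype coefficients or a 1-df per-allele test, chosen in advance.
2. Add one global haplotype test for the second primary objective.
3. Control the family-wise error over these six tests. Holm is simplest, with a first step at 0.05/6 = 0.0083. A max-T permutation that moves each subject's whole genotype row together makes use of the linkage and loses less.
4. Interpret individual coefficients only after their SNP has passed.
5. State the significance level, and state that the ANOVA and Kruskal–Wallis tests are descriptive.

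Report all other responses as exploratory, extending the investigational label already used in the Secondary objective section.

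The cost is a change of wording and some analysis code, plus lower power per SNP. Power should be restated at the adjusted level with the expected genotype counts, not with 55 per group. Under Hardy–Weinberg proportions with the article's Fok1 frequency, 158.4 completers split as follows:

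- 0.6715² × 158.4 = 71.4 common homozygotes
- 2 × 0.3285 × 0.6715 × 158.4 = 69.9 heterozygotes
- 0.3285² × 158.4 = 17.1 rare homozygotes

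In standard-deviation units, the standard error for rare against common homozygotes is √(1/17.1 + 1/71.4) = 0.269, against √(2/55) = 0.191 for two groups of 55, about 1.4 times as large. A power figure based on equal groups would therefore understate the loss for that contrast.

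The abstract places genotyping at the end of the study, so the change is best made before genotypes are linked to outcomes.

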### Approval and ethical considerations

The protocol was approved by the National Nutrition and Food Technology Research Institute (NNFTRI), Shahid Beheshti University of Medical Sciences (SBUM), Tehran, Iran (IR.SBMU.NNFTRI.REC.1395.62) (Registration ID in IRCT: IRCT2017091736244N1, registration date: 10-11-2017, http://www.irct.ir/trial/27153). All participants will be requested to sign a written informed consent at recruitment, in which trial procedures will be described. Participants will be informed that they have the right to withdraw from the study at any time.

## Discussion

The global cancer burden is expected to escalate about 47% by 2040, raising concerns regarding cancer prevention strategies [31]. The complex interplay between human genes and environmental exposures significantly contributes to the etiology of cancer. Dietary pattern and nutrients intake, as well as quantity and quality of diet, are reported to play a role in cancer development [32]. It has been indicated that the risk for developing cancer varies among individuals with similar dietary intakes, which could partly be explained by genetic variation in the form of SNPs, the most common genetic variation involved in nutrient genetic heterogeneity [32, 33]. Although pharmacogenetic testing, using gene polymorphism data to estimate drug transportation, metabolization, and requirements, has been applied to predict the efficiency of drugs, similar procedures have not been employed with nutrigenetics [34]. The study of genes and nutrition interaction will establish personalized nutrition that can enhance public health dietary recommendations [32]. It is believed that comprehension of genetic-based individualized response to dietary components will result in a more precise understanding of the exposure of intended tissue to dietary factors and their metabolites [35]

The strongest evidence for an association between genetic polymorphisms in VDR and health-related outcomes originates from the study by Abrams et al., in which the association between Fok1 polymorphism of *VDR* and bone mineral metabolism was documented [36]. Wong et al. in 2003 reported that individuals with the VDR Fok1 f allele manifested an elevated risk for colorectal cancer when dietary calcium intake is low [37]. It has been demonstrated that the *VDR* Fok1 f allele was associated with decreased calcium accumulation and increased bone problems [38]. Diets are a mixture of protective, carcinogenic, and mutagenic compounds metabolized via different types of enzymes in the human body [33]. Likewise, the effects of dietary elements on cancer risk may be modified by variations in genes involved in their transport and metabolism [39]. Millions of SNPs have been identified to modify multiple mutual relations of diet, genes, and health-related problems [40].

Most previous studies focused only on environmental aspects or the gene alone, but not on both simultaneously [33]. Hence, future studies using nutrigenomic approaches focused on genetic variation, diet, lifestyle, and environment to develop personalized nutritional strategies for cancer prevention and treatment are urgently needed.

To the best of our knowledge, this will be the first clinical trial being conducted to assess the role of *VDR* polymorphisms in individuals’ responses to vitamin D supplementation through assessing different aspects of cancer etiology, e.g., inflammatory, oxidative stress and metabolic biomarkers, biomarkers associated with cell proliferation, differentiation, damage, apoptosis, and anthropometric measures. Investigating different types of biomarkers will enable us to study the potential mechanisms and pathways through which vitamin D will be involved in cancer etiology and its related milieu. Response to vitamin D based on *VDR* polymorphisms will also be allowing us to scrutinize the gene and environment interactions simultaneously. The following will be the strengths of our study: first, the intervention will be carried out in the cold months, i.e., winter and early spring, when the endogenous synthesis of vitamin D is very low and due to the high prevalence of vitamin D deficiency in Tehran inhabitants [41], more noticeable response to vitamin D supplementation will be anticipated. Second, the results of the present study may illustrate the discrepancies that exist in the findings of different studies regarding vitamin D, VDR, and cancer by considering both genetic and environmental aspects simultaneously. If the response to vitamin D supplementation could be modified by VDR SNPs, determining the distribution of VDR polymorphisms in both breast cancer survivors and healthy populations will provide a new, much-needed insight on individual’s vitamin D requirements to prevent cancer and its related mortality based on the genotypes of these individuals. However, our study will be limited by the relatively small number of SNPs checked, which will likely represent only a small fraction of the variation in the VDR. In addition, the small sample size of the current investigation may result in lower statistical power. Furthermore, the 12-week trial may not be long enough to detect the anti-carcinogenic effects of vitamin D3. Finally, an absence of a control group will make it very difficult to attribute long-term changes in tumor markers to vitamin D3 per se.

## Data Availability

The datasets used during the current study will be available from the corresponding author on reasonable request.

## Abbreviations

BMI: Body mass index
VDR: Vitamin D receptor
IRCT: Iranian Registry of Clinical Trials
SNPs: Single-nucleotide polymorphisms
IU: International unit
25(OH) D_3_: 25-Hydroxy vitamin D_3_
MAF: Global minor allele frequency
OCP: Oral contraceptive pill
HER2: Human epidermal growth factor receptor 2
WC: Waist circumference
HC: Hip circumference
BIA: Bioelectrical impedance analysis
IPAQ: International Physical Activity Questionnaire
BSA: Body surface area
WBC: White blood cell
RFLP: Restriction fragment length polymorphism
ARMS: Tetra-amplification refractory mutation system
PCR: Polymerase chain reaction
TC: Total cholesterol
LDL-C: Low-density lipoprotein cholesterol
HDL-C: High-density lipoprotein cholesterol
TG: Triglycerides
ALT: Alanine aminotransferas
AST: Aspartate aminotransferase
IL6: Interleukin 6
TNFα: Tumor necrosis factorα
hs-CRP: Human high sensitivity C-reactive protein
IFNβ: Interferon β
TAC: Total antioxidant capacity
MDA: Malondialdehyde
8-OHdG: 8-Hydroxy-2′-deoxyguanosine
PAI-1: Plasminogen activator inhibitor-1
MMP9: Matrix metallopeptidase 9
SICAM-1: Soluble intercellular adhesion molecule-1
VCAM-1: Soluble vascular cell adhesion molecule-1
NNFTRI: National Nutrition and Food Technology Research Institute
SBUM: Shahid Beheshti University of Medical Sciences
